### Trial population

#### Screening data

All intubation encounters at participating sites will be assessed for eligibility for inclusion in the trial. The planned Consolidated Standards of Reporting Trials (CONSORT) [8] flow diagram will include all patients being screened for the study (Fig. 1). This will describe screened patients, those meeting exclusion criteria, eligible patients, consent process, those randomised into each of the study arms, with the documentation of the primary outcome. We will report on the start and stop date of the trial and provide the recruitment graph by month including division into the contributing sites as a supplementary figure.

**Fig. 1 Fig1:**
[figure not shown]
Proposed CONSORT participant flow diagram

#### Eligibility

Any patient undergoing endotracheal intubation in a participating department is eligible for inclusion. The specific inclusion and exclusion criteria are detailed in the protocol [4].

#### Withdrawal

If consent is not obtained or is withdrawn, data will be excluded from the analyses, unless permission is granted to use data recorded prior to the point of study withdrawal.

#### Baseline patient characteristics

Baseline characteristics (including demographic data, comorbidities, previous intubation details) at the time of randomisation will be reported for each of the two treatment groups (statistical comparison between groups will not be undertaken) (Table 1). Heart rate, respiratory rate and blood pressure will be presented as centiles, according to published charts [9, 10]. A supplementary table will be provided detailing additional baseline characteristics related specifically to the neonatal population.

**Table 1 Tab1:** Demographic and pre-intubation surgical characteristics of participants enrolled in the Kids THRIVE trial

Characteristic	Standard care, *N* =	THRIVE, *N* =
**Age at randomisation (years), ** *mean (SD)/median (IQR)*		
**Age at randomisation (years)** ^**a**^ **,** *n (%)*		
1 year		
1–7 years		
> 7 years		
**Weight (kg),** *mean (SD)/median (IQR)*		
**Female sex,** *n (%)*		
**Ethnicity,** *n (%)*		
Caucasian		
Aboriginal/Torres Strait Islander		
Asian		
African		
Indian		
Middle Eastern		
Māori		
Pacific Islander		
Others		
Unknown		
**Premature at birth (< 37 weeks),** *n (%)*		
**Intracardiac right-to-left shunt present at the time of intubation,** *n (%)*		
**Previous intubation,** *n (%)*		
**Cormack-Lehane laryngeal grade**		
Grade 1,* n (%)*		
Grade 2,* n (%)*		
Grade 3,* n (%)*		
Grade 4,* n (%)*		

*SD* standard deviation, *IQR* interquartile range, *MgSO*
_*4*_ magnesium sulphate

^a^Used for stratification

### Analysis

#### Outcome definitions

*Intubation attempt* is defined as a single advanced airway manoeuvre beginning with the insertion of the laryngoscope into the child’s mouth and ending when the laryngoscope is removed from the child’s mouth, or where there is a change in operator during the procedure even if the device is not removed.

*Hypoxaemia* is defined as transcutaneous oxygen saturations (SpO_2_) of ≤ 90% or a SpO_2_ saturation difference ≥ 10% for patients with cyanotic congenital heart disease with known substantial right-to-left shunts measured with the bedside monitor and with an accurate quality of the trace during the intubation attempt. Oxygen saturations will continue to be recorded for at least 2 min after the intubation attempt.

A *successful first attempt intubation* is defined as a successful placement of an endotracheal tube at first attempt, without any hypoxemia (SpO_2_ ≤ 90%or saturation difference ≥ 10% for right-to-left shunt). An unsuccessful first attempt intubation is either a successful first attempt intubation associated with hypoxemia, or requirement for more than one intubation attempt.

*Intubation attempt with rescue oxygenation* is defined as the provision of rescue oxygenation (for example, by bag and mask system) following an unsuccessful intubation attempt.

The following are the primary outcomes:

The clinically relevant and patient-centred outcome measures for intubation are hypoxemia and the number of attempts to achieve successful endotracheal intubation, both of which are strongly linked. Therefore, this study has two primary outcomes:Intubation attempt without hypoxaemiaSuccessful first attempt intubation

The following are the secondary outcomes:Number of intubation attemptsNumber of intubation attempts with rescue oxygenationLowest oxygen saturations during each attempt *(intubation attempt as unit of analysis)*
Lowest oxygen saturation in the 2 min immediately following an intubation attemptLowest oxygen saturation throughout total intubation encounter (defined as the first insertion of laryngoscope to successful intubation)Duration of invasive mechanical ventilation, defined as the start of successful intubation to extubationVentilation-free days (VFD), defined as the duration of respiratory support for all episodes with an ETT in situ for the first 28 days after randomisation censored at 28 days; VFD will be recorded as 0 in patients that died within 28 days after randomisationLength of ICU stay measured in days, defined as the start of successful intubation to ICU discharge, and limited to patients with an ICU admissionLength of hospital stay measured in days, defined as the start of successful intubation to hospital dischargeOccurrence of minor tracheal intubation-related adverse events (TIAEs) defined as one of the following in the period starting at the commencement of the intubation attempt until 2 min after successful intubation:Bradycardia, not requiring treatmentHypotension, not requiring treatmentMain stem bronchial intubationOesophageal intubation with immediate recognitionEmesis without aspirationEpistaxisDental or lip traumaOccurrence of major TIAEs defined as one of the following in the period starting at the commencement of the intubation attempt until 2 min after successful intubation:Cardiac arrest with or without return of spontaneous circulationOesophageal intubation with delayed recognition (> 60 s)Emesis with aspirationHypotension requiring treatmentBradycardia requiring treatmentLaryngospasmMalignant hyperthermiaPneumothorax or pneumomediastinumDeath, defined as death during current hospital admission

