### Statistical principles

The primary analysis will be conducted based on the intention-to-treat principle. Specifically, each randomised intubation encounter will be analysed based on the allocated treatment group, independent of compliance with the treatment delivered.

A per-protocol analysis including all intubation attempts where a study therapy was commenced (regardless of whether it was the therapy that was randomised) will also be undertaken and reported in the supplementary material.

The unit of analysis for most outcomes is the intubation encounter. If patients are required to be intubated more than once, they can be re-enrolled and re-randomised, theoretically receiving different study interventions for each intubation attempt within a single admission. For secondary outcomes relating to admission (i.e. ventilator-free days, length of ICU and hospital stay and death), only those patients with one enrolment per admission will be included in the primary and per-protocol analyses.

Statistical tests will be two-sided applying a statistical significance level of 0.05, although the primary outcomes will be analysed at a level of 0.025 (applying Bonferroni’s correction). We will not apply a formal correction for multiple testing to any of the subgroup analyses, sensitivity analyses or to the secondary outcomes. We will ensure conclusions drawn as a result of analyses are interpreted with deference to multiple comparisons.

If there is more than 10% of data missing for the primary outcomes, a sensitivity analysis using multiple imputation will be undertaken.

Continuous variables will be assessed for normality; this will be undertaken using visual inspection of histograms and *Q*-*Q* plots.

Descriptive statistics will be used when summarising variables; frequencies (percentages) for discrete variables, mean and standard deviation (SD) for normally distributed continuous variables, or, if continuous variables are non-normally distributed, median with interquartile range (IQR).

Subgroup analyses will be executed regardless of any potential treatment effect on the primary or secondary outcomes in the main cohort.

Changes to the analysis plan by the investigators effective after the publication of this SAP will be declared as such.

The statistical analysis will be undertaken using StataSE version 17 (StataCorp Pty Ltd., College Station, TX).

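### The failure definition for first-attempt success does not clearly cover a single failed attempt with no second, and ICU and hospital stay have no start time for a child who is never intubated

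*SAP article*

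**What the plan says.** All of the following stand in the SAP article, mostly under Outcome definitions.

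- **Success on the second primary outcome** "is defined as a successful placement of an endotracheal tube at first attempt, without any hypoxemia".
- **Failure** is defined separately: "An unsuccessful first attempt intubation is either a successful first attempt intubation associated with hypoxemia, or requirement for more than one intubation attempt".
- **An attempt** does not need to succeed in order to end; it is described as "ending when the laryngoscope is removed from the child’s mouth, or where there is a change in operator during the procedure". The rationale for the two primary outcomes, however, speaks of "hypoxemia and the number of attempts to achieve successful endotracheal intubation", which takes eventual success for granted.
- **Duration of invasive ventilation, ICU stay and hospital stay** all begin at successful intubation. Under Secondary outcome measures, the two stays are analysed with Cox models.
- **The window for the lowest saturation over the whole encounter** is "defined as the first insertion of laryngoscope to successful intubation".
- **Minor and major intubation-related adverse events** are counted "in the period starting at the commencement of the intubation attempt until 2 min after successful intubation".
- **Ventilation-free days** are different: they are counted "for the first 28 days after randomisation censored at 28 days".
- **Statistical principles** states that "each randomised intubation encounter will be analysed based on the allocated treatment group, independent of compliance with the treatment delivered".

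**The concern.** A binary primary outcome should classify every encounter whose result is known. Here success and failure are each defined, and the two definitions do not add up to the whole. What falls between them is a single kind of encounter: the only attempt fails and no further attempt follows. Every such encounter is a non-success, so how it is coded always matters in the same direction within an arm, and it affects the comparison if its frequency differs between arms. The choice should be fixed before the data are seen.

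For the stays the difficulty is a stated rule rather than a loose sentence. Starting the clock at successful intubation conditions the analysis on something that happens after randomisation and that the intervention could influence. The plan does restrict the admission-level outcomes openly (to patients with one enrolment per admission, and ICU stay to those admitted to ICU). The exclusion of never-intubated children follows only from the choice of start time and is not declared.

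**Working it through.** **1. Classify every kind of encounter under the two definitions.**

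| First attempt | What follows | Success? | Failure, branch 1 (tube placed, with hypoxaemia)? | Failure, branch 2 (more than one attempt required)? |
|---|---|---|---|---|
| Tube placed, no hypoxaemia | – | Yes | No | No |
| Tube placed, hypoxaemia | – | No | Yes | No |
| Not placed | Second attempt made | No | No | Yes |
| Not placed | No second attempt, tube still needed | No | No | Only if requirement means need rather than attempts made |
| Not placed | No second attempt, tube no longer needed | No | No | Does not fit |

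Hypoxaemia during the failed attempt does not settle the last two rows, because branch 1 covers only attempts that placed a tube.

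**2. Check the other outcomes for a child never intubated.**

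- Ventilation duration, ICU stay, hospital stay: no start time.
- Encounter lowest saturation, adverse-event windows: a defined start, no defined end. Events during the attempt are inside the window.
- Hypoxaemia during the attempt, number of attempts, saturation per attempt, ventilation-free days, death in hospital: defined.

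**3. Reproduce the plan's own figures (Sample size).** Two-sided alpha 0.025, power 90%, 1:1, pooled variance, no continuity correction:

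n per arm = [z(0.9875)·√(2p̄(1−p̄)) + z(0.90)·√(p1(1−p1) + p2(1−p2))]² / (p1−p2)²

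- 16% vs 8%: 408 per arm, 816 in total. Matches.
- 60% vs 80%: 129 per arm, 258 in total. Matches.
- 816 / 0.85 = 960. Matches.

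**4. Size of the coding choice on the second primary outcome.** The share of encounters abandoned after one failed attempt is not in the document. Assume 0.5% to 3% per arm, and take the planning rates of 60% and 80% as holding among all other encounters. Leaving the abandoned encounters out gives an odds ratio (OR) of (0.80/0.20)/(0.60/0.40) = 2.67. Counting them as failures gives success of 0.60(1−q) in control and 0.80(1−r) in THRIVE, where q and r are the abandoned shares. For q = 1% and r = 3% this is 0.594 and 0.776, so OR = (0.776/0.224)/(0.594/0.406) = 2.37.

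| Abandoned, control / THRIVE | Encounters of 960 | OR, counted as failures | Total N for this outcome |
|---|---|---|---|
| 0.5% / 0.5% | about 5 | 2.63 | 262 |
| 1% / 1% | about 10 | 2.60 | 266 |
| 2% / 2% | about 19 | 2.54 | 274 |
| 3% / 3% | about 29 | 2.49 | 284 |
| 1% / 3% | about 19 | 2.37 | 320 |
| 3% / 1% | about 19 | 2.74 | 238 |

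Power for this outcome at 408 per arm stays above 99.9% in every row.

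**5. The same on the difference scale, with a smaller true effect.** Assume true success of 60% and 65% over all encounters, with 2% abandoned in control and 0.5% in THRIVE. Leaving those out gives 0.60/0.98 = 61.2% and 0.65/0.995 = 65.3%. The difference is 4.1 points instead of 5.0.

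**6. The stays.** The document gives no figures from which the effect on ICU or hospital stay could be computed.

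**The case against.** A reader might infer that abandoned encounters drop out of the primary analysis and that intention-to-treat is broken there. The document does not say that. Success is defined positively and completely, and an abandoned attempt plainly does not meet it. Statistical principles requires every randomised encounter to be analysed, the model is a logistic regression of a binary outcome, and Table 3 reports the outcome for the total trial cohort. Together these point to coding the encounter as a failure. The second branch also speaks of a requirement for more than one attempt, which can cover a child who still needed a tube. Nor is this missing data: an abandoned attempt can be seen on the case report form or video, so the imputation rule does not apply. All of this stands. What remains is that the failure sentence offers a closed list, and that list does not fit a child who no longer needed a tube.

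A reader might also infer that major adverse events in these children go uncounted. They do not: the window opens when the attempt begins, so an arrest or aspiration during it is captured, and only the closing time is open. Death has its own definition, tied to the hospital admission.

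It is also fair to say that a never-intubated child has no ventilation episode to time, that the stays are secondary outcomes without p-values, and that such encounters are probably rare. These points limit the size of the problem. They do not supply a start time for the stays.

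**Conclusion.** The point holds in a limited form. For the second primary outcome it is a gap in wording: success and failure are not complements, and the likely coding has to be inferred. For ICU and hospital stay it is a stated rule that leaves never-intubated children out of the Cox models, against the plan's own principle and without being declared as a restriction.

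The expected effect is small. The shifts shown (odds ratio 2.67 against 2.37 to 2.74; 5.0 against 4.1 points) rest wholly on assumed abandonment rates, and the larger ones also need a marked imbalance between arms. They describe what would happen if the encounters were excluded, which the text does not direct. The planned sample size, power, the hypoxaemia outcome, ventilation-free days and death are unaffected.

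**What to change.** Four changes of wording:

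1. Define an unsuccessful first attempt as every randomised encounter that does not meet the success definition, expressly including those that end without a tube. Encounters whose result was not recorded stay under the Missing data section.
2. Start ICU stay and hospital stay at randomisation, as ventilation-free days already do.
3. State that duration of invasive ventilation does not apply to a child who is never intubated, and report how many there are in each arm.
4. When no tube is placed, close the encounter lowest-saturation window and the adverse-event windows 2 min after the last attempt.

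The cost is a declared amendment to the SAP text. The article does not list randomisation time among its data items, but ventilation-free days already depend on that anchor, so a usable date or time must exist. For intubated children the stays should change only by minutes, since the envelope is opened once the operator for that intubation has been chosen.

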##### Secondary outcome measures

Binary outcome measures (e.g. occurrence of AE) will be treated in the same manner as the primary outcome; however, no *p*-values will be reported (Table 3). Similar analyses will be undertaken for continuous outcomes: linear regression with adjustment for the treatment group and stratification variables as fixed effects and site and patient as random effects, with reporting of mean difference (unadjusted for stratification variable and adjusted) and 95% CIs. If necessary, quantile regression will replace linear regression in the instance of highly skewed data. Survival outcomes (length of PICU stay, length of hospital stay) will be visually presented using a Kaplan–Meier plot, and a Cox proportional hazard model will be used to assess the differences between the treatment groups with treatment group and stratification variables as fixed effects and site and patient as random effects (i.e. utilising a shared frailty model). The proportionality assumption will be inspected visually using Kaplan–Meier plots and the log–log plot. The hazard ratio and 95% CI will be presented as an estimate of treatment effect. Competing-risk regression will be used to analyse VFDs (competing risk of mortality with duration of ventilation). The lowest oxygen saturation during each intubation encounter will be reported in-text using each encounter as the unit of analysis (and as such incorporating intubation episode as a further random effect into the model). Key assumptions of the models (for logistic regression: specification, goodness-of-fit, absence of multicollinearity and absence of influential observations; for survival analysis: proportionality assumption, goodness-of-fit; for linear regression: specification, distribution of residuals, homoscedasticity, absence of multicollinearity, linearity) will be tested and reported on.

**Table 3 Tab3:** Primary outcomes in the total trial cohort and subgroups as per intention-to-treat analysis

	**Standard care, ** ***N*** ** = **	**THRIVE, = **	**Estimate of difference (95% CI)***	**Adjusted estimate of difference (95% CI)** ^**a**^	***p*** **-value**
**Outcome: hypoxic event** *Oxygen saturations (SpO* _*2*_ *) of* ≤ *90% or a SpO* _*2*_ * saturation difference* ≥ *10% for patients with cyanotic congenital heart disease with known substantial right-to-left shunts*					
**Total trial cohort,** * n (%)*					

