#### Adverse events and protocol deviations

All adverse events defined in the study protocol will be reported as described in Table 3 and compared between the two study groups using logistic regression as described above for secondary outcomes (Table 4). Protocol deviations will be tabulated and reported in the supplementary material.

**Table 4 Tab4:** Secondary outcomes in the total trial cohort

Outcome	Standard care, *N* =	THRIVE, *N* =	Estimate of difference (95% CI)^a^	Adjusted estimate of difference (95% CI)^b^
Number of intubation attempts, *median (IQR)*				
Number of intubation attempts with rescue oxygenation, *median (IQR)*				
Lowest oxygen saturation throughout total intubation period, *median (IQR)*				
Duration of mechanical ventilation, *median (IQR)*				
Ventilation free days, *median (IQR)* ^c^				
Length of ICU stay (days), *median (IQR)* ^c,^ ^d^				
Length of hospital stay (days), *median (IQR)* ^c^				
Minor adverse events				
Bradycardia, not requiring treatment,* n (%)*				
Hypotension, not requiring treatment,* n (%)*				
Main stem bronchial intubation,* n (%)*				
Oesophageal intubation with immediate recognition,* n (%)*				
Emesis without aspiration,* n (%)*				
Epistaxis,* n (%)*				
Dental or lip trauma,* n (%)*				
Major adverse events				
Cardiac arrest with or without return of spontaneous circulation,* n (%)*				
Oesophageal intubation with delayed recognition (> 60 s),* n (%)*				
Emesis with aspiration,* n (%)*				
Hypotension requiring treatment,* n (%)*				
Bradycardia requiring treatment,* n (%)*				
Laryngospasm,* n (%)*				
Malignant hyperthermia,* n (%)*				
Pneumothorax or pneumomediastinum,* n (%)*				
Death during current hospital admission, *n (%)* ^c^				

*SD* standard deviation, *IQR* interquartile range, *CI* confidence interval

^a^Adjusted for study site only

^b^Adjusted for age at randomisation, operator level and study site

^c^Limited to those patients with one enrolment per admission or multiple enrolments receiving the same randomised treatment

^d^Patients with an ICU admission only

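### Ventilation-free days are defined as days with a tube in place, yet death scores 0, so a death ranks better than any ventilated survivor

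*SAP article*

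**What the plan says.** Four places in the SAP bear on this outcome.

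- **Outcome definitions, secondary outcomes.** VFD is "defined as the duration of respiratory support for all episodes with an ETT in situ for the first 28 days after randomisation". The sentence goes on to apply a 28-day censoring limit and to give a value of 0 to any child who dies inside that window.
- **The same list.** Duration of invasive mechanical ventilation, from successful intubation to extubation, is a separate secondary outcome.
- **Secondary outcome measures.** "Competing-risk regression will be used to analyse VFDs (competing risk of mortality with duration of ventilation").
- **Table 4.** VFD has its own row, summarised as median (IQR) by arm, with unadjusted and adjusted estimates of difference. The table has no p-value column. Duration of mechanical ventilation has another row.

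Nowhere does the SAP subtract the tube time from 28 or say whether a high or a low value is favourable.

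**The concern.** The name, the definition and the death rule do not describe the same variable. The name means days free of the ventilator, where more is better. The definition measures days on the ventilator, where fewer is better. Scoring death as 0 agrees with the name, because 0 free days is the worst result, but conflicts with the definition, because 0 tube days is the best.

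If the derivation follows the text, a death counts as less ventilation than any ventilated survivor had. If the analyst instead takes the label at face value and treats high as good, 28 days of unbroken ventilation becomes the best possible result. Either way, the Table 4 row would mislead. Length of mechanical ventilation is one of the stated secondary objectives, and VFD is the only ventilation outcome whose definition takes account of death.

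The model is a second mismatch. Competing-risk regression needs a time on ventilation and a time of death. A score that has already replaced the child's value with 0 at death supplies neither.

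**Working it through.** The SAP gives no figure for this outcome to reproduce, so the check applies its two scoring rules to example children and compares the result with the score that the name implies.

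**Inputs.** From the SAP: the 28-day window, the tube-time definition and the value of 0 for death. Assumed for illustration: the days *d* with a tube in place, and the mortality *m* used below.

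**Formulas.**
- As written: L = min(d, 28) if alive at day 28; L = 0 if dead.
- As named: V = 28 − min(d, 28) if alive at day 28; V = 0 if dead.

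| Child | L, as written | V, as named |
|---|---|---|
| Extubated after 1 hour | 1/24 = 0.04 | 28 − 0.04 = 27.96 |
| Ventilated 2 days | 2 | 26 |
| Ventilated 3 days | 3 | 25 |
| Ventilated 5 days | 5 | 23 |
| Ventilated 14 days | 14 | 14 |
| Ventilated 28 days | 28 | 0 |
| Died on day 5 | 0 | 0 |

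In the L column, survivors do better as the score falls, and the death sits below all of them, including the child extubated after an hour. In the V column, higher is always better and death ties with the worst survivor.

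**Effect on an arm's mean.** Suppose every survivor is ventilated for 5 days. Then mean L = (1 − m) × 5 and mean V = (1 − m) × 23.

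| Assumed mortality m | Mean L | Mean V |
|---|---|---|
| 5% | 0.95 × 5 = 4.75 | 0.95 × 23 = 21.85 |
| 10% | 0.90 × 5 = 4.50 | 0.90 × 23 = 20.70 |
| 20% | 0.80 × 5 = 4.00 | 0.80 × 23 = 18.40 |

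As written, more deaths look like less ventilation. As named, more deaths make the result worse, as they should.

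**Effect on the median that Table 4 reports.** With a fraction m of values at 0 under L, the overall median falls at survivors' quantile (0.50 − m)/(1 − m). For m = 5% this is 0.45/0.95 = 0.47, and for m = 10% it is 0.40/0.90 = 0.44. Deaths at these rates therefore move the median only modestly. The larger fault in that row is its direction: a median of ventilated days would stand under a label that says free days.

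**Score against model.** The definition removes death as an event by turning it into a value of 0. The methods section treats death as an event competing with ventilation. Both are usable, but on different variables, and the SAP calls both VFD.

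**The case against.** The best defence is that this is a drafting slip with a recoverable meaning. The name and the death rule both point to 28 minus ventilated days, and ventilated time already has its own outcome and its own table row. A reversed result would require a programmer to ignore the variable's name. That is fair, and it lowers the severity. It does not clear the text: the definition is explicit, it contradicts both its name and its death rule, and an analyst has to choose which to follow.

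Several stronger readings are tempting, and the document does not support them.

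- *Every death becomes a competing event at time 0, and the date of death is lost.* This assumes that the VFD score is the model's time variable. The methods section names duration of ventilation as the modelled quantity, and censoring at 28 days suits that reading. What stands is narrower: the SAP does not separate the score from the model's time variable.
- *A countable number of children per arm would be misplaced.* The SAP gives no mortality. The 960 encounters include the attrition allowance (816 without it), and the Statistical principles section restricts admission-level outcomes further. The analysed number is not stated, so no count can be given.
- *Death is scored like a child who was never ventilated.* Enrolled children are being intubated, so that is only a limiting case. The relevant comparison is with ventilated survivors.
- *Competing-risk regression must be abandoned.* It is coherent for time on ventilation with death at its own time. An ordinal or rank-based model for the score is an option.

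Also, deaths could favour one arm only if mortality differed between arms, and death has its own row in Table 4, where a difference would be visible.

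**Conclusion.** The definition is wrong as written. It describes the complement of the named outcome and, combined with a value of 0 for death, ranks a death ahead of every ventilated survivor. That conclusion rests on the SAP's own wording and needs no assumed figure; the mortality rates and the 5-day duration above only illustrate the direction. The competing-risk analysis also needs to be separated from the score.

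A reader might infer that the trial's ventilation result is bound to come out reversed, or that its main conclusions are at risk. Neither follows. The intended direction can be inferred, the effect is limited to one secondary outcome without a planned p-value, and neither the sample size nor the interim criterion depends on it. It should be fixed, and it is not critical.

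**What to change.** 1. In Outcome definitions, define VFD as 28 minus the total days with an endotracheal tube in place from randomisation to day 28, summed over all episodes, with a minimum of 0 and a value of 0 for death by day 28. State that higher is better.
2. Use this score for the Table 4 median (IQR) and for its estimate of difference. An ordinal or rank-based model is one option for that estimate.
3. In Secondary outcome measures, state separately that the competing-risk regression models time on ventilation to extubation, censored at 28 days, with death entered as the competing event at its actual time and not as 0. Label its result as time on ventilation, not as VFD.

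The cost is a few sentences and the derivation code. Ventilation start and stop times already come from the registry extract described under Data sources, so no new data source is needed. The Statistical principles section already provides for declaring changes made after publication.

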### Sample size

A conservative estimate of the primary outcome of hypoxaemia is set at 16%, following an unpublished 2016 audit of data from the Queensland Children’s Hospital, which we found was comparable to a published report [1]. Assuming a clinically relevant effect size of a 50% reduction in the proportion of desaturation events from 16 to 8%, along with a type I error of 0.025 (adjusting for two primary outcomes using Bonferroni’s correction) and power of 90%, 816 intubation encounters in total are required. Successful first-attempt intubation, the second primary outcome, assumes an absolute increase from 60 to 80%, requiring 258 intubation encounters. Allowing for 15% attrition, the total sample size that will satisfy both primary outcome measures is 960 intubation encounters. An attrition rate of 15% was selected based on the assumption that a proportion of patients enrolled will have a clinical deterioration, or other clinical events, during a high-stress procedure leading to the inability to deliver the intervention or collect the outcome data required for the study.

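### Ventilation-free days are defined as days with a tube in place while death scores 0, so the Table 4 summary of this secondary outcome would run backwards among survivors

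*SAP article*

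**What the plan says.** Three places in the SAP article bear on this outcome.

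- **Outcome definitions.** VFD is "defined as the duration of respiratory support for all episodes with an ETT in situ for the first 28 days after randomisation", and the count stops at day 28. The sentence goes on to assign 0 to any child who dies within 28 days of randomisation. The item listed just before it is a separate secondary outcome, the duration of invasive ventilation from intubation to extubation.
- **Secondary outcome measures.** "Competing-risk regression will be used to analyse VFDs (competing risk of mortality with duration of ventilation").
- **Table 4** (under Adverse events and protocol deviations). A row labelled "Ventilation free days" is summarised by arm as a median with interquartile range, alongside separate rows for duration of ventilation and for death. The table has no p-value column.

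**The concern.** The name of the outcome and its rule for deaths point one way, and its formula points the other. On a free-days scale more is better and 0 is the worst result, so scoring a death as 0 makes sense. On the scale that the sentence describes, more is worse and 0 means no ventilation at all, so scoring a death as 0 puts the worst outcome at the favourable end.

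A programmer who follows the sentence would produce a variable with no consistent direction: high values are bad among survivors, yet deaths lie at the bottom. A reader of a row headed as ventilation-free days will take higher as better. Length of ventilation is among the trial's stated secondary objectives, and VFD is the outcome meant to combine it with survival.

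**Working it through.** **The plan's own figures.** The SAP gives no number for VFD, so there is none to reproduce. Its sample sizes do reproduce: 16% versus 8% and 60% versus 80%, two-sided alpha 0.025, power 90%, 1:1, pooled variance and no continuity correction give 816 and 258 encounters, and 816 / (1 − 0.15) = 960. VFD does not enter that calculation.

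**Step 1: apply the written rule to single patients.** Let *v* be days with an ETT in situ within 28 days.

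- As written: score = min(*v*, 28), or 0 if the child dies by day 28.
- Free-days form: score = 28 − min(*v*, 28), or 0 if the child dies by day 28.

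The second form is inferred from the outcome's name and its death rule. The article does not state it. The patients are illustrative.

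| Patient | As written | 28 minus ETT days |
|---|---|---|
| Survivor, extubated at 6 h | 0.25 | 27.75 |
| Survivor, 2 ETT days | 2 | 26 |
| Survivor, 10 ETT days | 10 | 18 |
| Survivor, ventilated all 28 days | 28 | 0 |
| Died on day 5 or day 20 | 0 | 0 |

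As written, survivors are ranked in reverse. Deaths are a quarter of a day from the earliest extubation and 28 points from the survivor ventilated throughout. In the free-days form, a death ties with the survivor ventilated throughout, as the death rule implies.

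**Step 2: the effect on the planned summary.** Assume 5% mortality in both arms, with every survivor ventilated for 3 days in one arm and 8 in the other. Fewer than half of the children score 0, so each median is the survivor value.

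- Median as written: 3 versus 8.
- Median in the free-days form: 28 − 3 = 25 versus 28 − 8 = 20.

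Means, with *d* for mortality, behave in the same way.

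- As written, (1 − *d*) × *v*: 0.95 × 3 = 2.85 versus 0.95 × 8 = 7.60.
- Free-days form, (1 − *d*) × (28 − *v*): 0.95 × 25 = 23.75 versus 0.95 × 20 = 19.00.

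The arm with shorter ventilation shows fewer free days as written and more in the free-days form.

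**Step 3: a difference in mortality alone.** Assume 5 ventilated days among survivors in both arms, and mortality of 5% versus 10%.

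- Mean as written: 0.95 × 5 = 4.75 versus 0.90 × 5 = 4.50.
- Mean in the free-days form: 0.95 × 23 = 21.85 versus 0.90 × 23 = 20.70.
- Median: 5 in both arms as written, and 23 in both arms in the free-days form.

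Table 4 plans a median, so this example would show nothing there.

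**Step 4: set the definition beside the model.** The competing-risk regression is described in terms of ventilation duration, with death as the competing event. It needs the time at which ventilation ended or the child died. A child who dies on day 20 has a time of 20 days in that model but a score of 0 under the definition. The score cannot be the model's input, and the model description does not supply the missing subtraction.

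**The case against.** The strongest reply is that the intended meaning can be recovered. The label says ventilation-free, the death rule works only on a free-days scale, and ventilated time is already a separate outcome. The sentence has probably just lost its subtraction, and the protocol, which is not shown, may have it right. That is a fair account of how the error arose, but the SAP states the derivation rule, and nothing in the article corrects it.

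Three stronger readings are tempting and are not supported.

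- *The treatment estimate is reversed whichever model is used.* The SAP plans a competing-risk regression on ventilation duration with death as a competing event. Its estimate depends on times and event types, not on the score, and need not change sign. The median and interquartile range are what take their direction directly from the score.
- *Higher mortality would appear in Table 4 as less ventilation.* That pattern appears in means (4.75 versus 4.50), but the planned summary is a median, which is 5 in both arms of that example.
- *A death scores the same as an immediate extubation.* It is a near-tie. Enrolled children are undergoing intubation, so a survivor would normally score above 0, as the value of 0.25 at 6 hours shows.

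It is also true that ventilation duration and death have their own rows in Table 4, so a reversed VFD row would visibly clash with its neighbours. That makes the error easier to notice, but does not remove it.

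**Conclusion.** The definition is wrong as written. It counts ventilated days under the name of ventilation-free days, and its death rule fits only the opposite scale. Programmed literally, the Table 4 median and interquartile range would run backwards among survivors and place deaths beside the best of them. In the illustration, the medians become 3 versus 8 where 25 versus 20 was presumably meant. The size rests on assumed durations and mortality, since the SAP gives none. The direction among survivors follows from the wording alone. The competing-risk estimate need not reverse, but it is inconsistent with coding deaths as 0.

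A reader might infer that the trial's main conclusions are at risk. They are not. VFD is one secondary outcome with no p-value column in its table, and it bears on neither primary analysis nor on the sample size. This is a correction to make before analysis, not a threat to the trial.

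**What to change.** 1. In Outcome definitions, define VFD as 28 minus the total days with an ETT in situ, over all episodes, in the 28 days after randomisation, with a minimum of 0. Set it to 0 if the child dies within those 28 days. State that higher is better.
2. Use this score for the median and interquartile range in Table 4.
3. In Secondary outcome measures, state that the competing-risk model uses the actual times to end of ventilation and to death, not the score with deaths set to 0. Changing the definition alone would leave the score and its analysis mismatched.
4. Check the wording against the protocol, and declare the change, as the Statistical principles section promises for changes made after publication.

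The cost is a sentence in each of two sections and a small change to the derivation code. No new data are needed.
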